### Intervention strategy

#### Cash transfer value

The intervention is a conditional cash transfer (CCT) payment for each facility appointment attended for ANC, delivery, postnatal care and childhood immunization; and referrals related to any of these visits. For each verified health visit that is made on time following enrolment, a woman receives a cash transfer of Ksh 450 (4.5 USD). The value reduces by one quarter for each week of delayed visit, and no reward is offered for any visit made 3 weeks after the appointment date. On average, Ksh 450 equates to the transportation cost of a local taxi to the health facility, and is a value that has been approved by the research ethics committee for many studies in the region as reasonable compensation for research participants.

#### Card-reader system for automatic tracking of health visits and cash transfers

##### *Afya* card

Once consent to participate in the trial is obtained, all women recruited into the study are given an ANC clinic book as is standard practice. Additionally, they are provided with a special enrolment card (*Afya* card) that contains their study ID and that is linked to a card reader terminal installed at all participating health facilities. The card is attached to the clinic book so that participants do not leave it behind when making the health visits.

The *Afya* card is the size of a credit card and stores holder data. These include authentication information (study ID, study arm, clinic at which enrolled), pregnancy-related information (pregnancy stage at enrolment, expected delivery date (EDD), parity) and information on health visits made (where and when) throughout the study period. The background and pregnancy-related information is collected at enrolment by a nurse at the clinic, who then loads it onto the card upon touching the card to the reader. The nurse also keys in the date of enrolment and the date of the next visit, which gets loaded onto the card upon touching the reader. Subsequent health visits by participants are recorded in their clinic books and the clinic records as is standard practice (Additional file 2). Additionally, the visits are automatically tracked by touching the card on the card reader. At the end of each visit, the nurse keys into the reader the date of the next health visit, to enable automatic tracking of whether the visit is attended and how timely the visit was.

##### Card reader

Card readers are installed in all participating intervention and control facilities. The device used is a Famoco Fx100, an android near field communication (NFC) card reader. The Fx100 has an in-built SIM card slot and is enabled for GSM/GPRS/3G communication. The card reader is connected to a remote server that electronically personalizes the NFC card of the user during enrolment, and tracks her subsequent health visits. Each time the *Afya* card makes contact with the reader, the information stored on the card is transmitted to the reader and from the reader to the card, then subsequently from the reader to the web portal (an electronic database) [29]. The card also has an offline transacting capability with the terminal reader that enables it to function during occasional absence of connectivity. The reader also comes with a power back up that enables it to function when there is no electricity for a prolonged duration.

This web portal enables the study team to remotely track participants’ health facility attendance throughout pregnancy and up until 12 months after delivery, and to effect the cash transfer payments. On confirmation of a timely visit, payments to participants are made directly from the project’s bank account where the funds are held, to the participants’ mobile money accounts. This is achieved through integration of the Famaco FX card reader system with Safaricom Bulk Disbursement Service, the leading mobile money payment provider in Kenya. A payout is thus automatically triggered following the touching of the *Afya* card on any of the 48 terminal readers. Manual payouts are triggered by the project team upon verification of visits by participants who forget to carry their clinic books during the visits or who visit non-enrolling facilities that have no readers installed. Pregnant women are therefore not restricted to using the facility at which they were enrolled as long as it is within the study evaluation zone, which is Siaya County. Health visits outside Siaya County are not recorded or rewarded, except for high-risk groups (see Collecting data on visits to facilities outside the study area).

The web portal is continually monitored by a member of the project team to ensure that there are no pending payments for timely health visits attended. The project team also makes regular visits to the health facilities to monitor whether all system components function as expected, and to resolve any challenges promptly.

#### Gratuity for control group participants

Although the primary function of the cash transfer is to motivate health facility visits, the cash payment could additionally motivate women in the intervention group to carry their ANC clinic books when they visit the clinics. This is because the *Afya* card embedded in the book facilitates automated payment transfers to the women at the end of the clinic visit. Forgetting to carry the ANC clinic card during ANC visits delays the payment as the visit must be verified manually. Therefore, to balance out the possible health effects of carrying the ANC clinic book in the intervention and control groups, a nominal gratuity for carrying the clinic book is offered to women in the control group, who might have lower motivation to carry the book. The gratuity is in the form of mobile phone airtime with a value of Ksh 50 (0.5 USD) for every eligible visit, transferred through the same system that is used to issue the incentives. Ksh.50 is approximately equivalent to the cost of five bananas purchased at a market and would not compensate participants for the cost of attending the health visit. It may however, be an incentive for a woman who was going to go to the clinic anyway, to carry her clinic book.

Participants in both study groups are followed up in the same way, including monitoring of visits using the electronic-based system and telephone surveys conducted at key points in the care continuum. Follow up is described Data collection methods.

#### Health staff incentives

Trained and incentivized health staff determine if a pregnant woman meets the study eligibility criteria by administering screening questions at the end of her ANC visit. Health staff also collect background information on participants and key it into the card reader. During subsequent visits, staff key in the next visit dates on the readers to enable electronic tracking of whether the visit was attended and when it was attended. This determines the amount of cash incentive the participant receives. Staff are paid 400 Ksh (about 4 USD) per person enrolled into the trial, to recognize their time and effort in enrolling participants and tracking subsequent health visits.

#### Theory of change

The intervention’s theory of change [30] is described in Fig. 2 and is informed by the World Health Organization (WHO) guidelines for health visit schedules for women during pregnancy, birth and the postnatal period [4]. Extensive evidence supports the health benefits of services offered during these visits [4] (Additional file 4).

**Fig. 2 Fig2:**
[figure not shown]
Theory of change. MNCH, maternal, newborn and child health; ANC, antenatal care; PNC, postnatal care; EBF, Exclusively breastfeeding

The rationale for the use of a CCT intervention is found in behavioural economic theory, which suggests that individuals commonly have inconsistent preferences for similar outcomes occurring at different points in the future, with outcomes in the near future generally valued more than those in the distant future [31, 32]. According to Giles et al. [33], while the health gains of health-promoting behaviours are often delayed in time, the financial and opportunity costs are usually immediate. Individuals thus make a rational choice to pursue unhealthy behaviours or delay spending on health-promoting activities in the present but with future benefits. Cash transfers work by bringing long-term goals into the short-term decision horizon by providing immediate rewards and reducing current costs [33].

This study is based on the theory that cash transfers overcome direct and indirect financial and behavioural barriers to healthcare attendance during pregnancy, delivery and the postnatal period, and in so doing would lead to more regular use of services compared to current practice. Retention of women in the care continuum from pregnancy through the postnatal period will have a positive impact for MNCH interventions that require regular treatment and follow up.

### Research questions

This study aims to investigate whether CCTs are effective in retaining women in the continuum of care for MNCH. The secondary objectives of the study aim to establish whether regular care-seeking within the MNCH continuum, incentivized by the CCTs, leads to improved maternal and child health outcomes and whether it can be cost-effective. To answer these questions, a number of primary and secondary outcomes will be measured.

#### Primary outcomes

The following primary outcomes will be measured and compared between the two study arms:The proportion of eligible ANC visits made after recruitmentThe proportion of participants delivering babies at a health facilityThe proportion of eligible health appointments attended for PNCThe proportion of expected immunization appointments attended by childrenThe proportion of health referrals attended for ANC, PNC and child immunization

#### Secondary outcomes

The secondary outcomes are:Proportion of women retained in the continuum of MNCH from pregnancy to 12 months post-deliveryLikelihood of a live birth and child survival 48 h after birthLikelihood of maternal death during delivery and 48 h postpartumSelf-rated health of mothers at 6 months and 12 months after deliveryMother’s perception of infant’s health 6 months and 12 months after deliveryProportion of mothers exclusively breastfeeding to 6 months of ageProportion of women using family planning or contraceptives after deliveryScreening and control of infections for mothers and fetus/baby during pregnancy and postnatal periodsCost of delivery and cost effectiveness of the interventionBenefit incidence and equity impact of the intervention

Process evaluation [34] will document the design, implementation and mechanisms of the intervention. A full economic evaluation will be conducted to assess the cost of delivery and cost effectiveness of the intervention and the benefit incidence and equity impact of trial activities and outcomes.

### Sample size

We hope to analyse all the primary outcomes jointly and also to analyse most outcomes as ordinal variables (see Data management and analysis), thereby maximising power and aiding interpretation. However, for our sample size calculation, we consider power to detect an effect of the intervention on one primary outcome, which we also assume to be a binary indicator that all attendances are made, as this is simple and conservative in the power achieved. The expected prevalence of these indicators in the control arm ranges between 30 and 80%. Little specific information on the likely intra cluster correlation (ICC) for any of the outcomes is currently available - we consider it may lie between 0.005 (low) and 0.025 (moderate). Our planned sample size is 48 clusters (24 per arm) and an average cluster size of 150. At a low ICC, the design effect (DE) will be 1.745 and hence the effective sample size (ESS) will be 2063 participants per study arm. At a moderate ICC, the DE will be 4.725 and hence the ESS will be 762 per arm. Power to detect absolute differences is lowest when the prevalence is 50% and highest when the prevalence is either high (towards 100%) or low (towards 0%). Here we consider the prevalence in the control arm to range between 50% (‘worst-case scenario’) and 80% (‘best-case scenario’). We consider the standard 5% significance level. If the prevalence of the outcome is 50% in the control arm, the sample size provides 80% power to detect an improvement to 54.5% in the intervention arm if the ICC is low and 57.5% if the ICC is moderate. If the prevalence of the outcome is 80% in the control arm, the sample size provides 80% power to detect an improvement to 83.5% if the ICC is low and 85.5% if the ICC is moderate.

### Data collection methods

Data are collected in person by nurses at enrolment, over the telephone by trained interviewers at key time points, and through manual extraction of routine health records supplemented by the electronic contact card system. Data are also collected to facilitate rigorous process and economic evaluations. Table 1 summarizes the data collected using each method.

**Table 1 Tab1:** Primary and secondary outcomes of the trial and sources of these data for different outcomes

Primary outcomes	Source of data
• Proportion of all eligible ANC visits made after recruitment • Delivery at a health facility • The proportion of health appointments honoured for PNC at week 2 to 6 after delivery, and months 4–12 after delivery • Proportion of referrals for ANC, PNC and child immunization attended Proportions of immunization appointments attended by children	• Abstracted health records from the health facility • Electronic system used to enrol participants into the study • Telephone surveys will collect visits made outside the study area by all “high risk” women and 50% of other women
Secondary outcomes	Source of data
• Proportion of women retained in the continuum of MNCH from pregnancy to 12 months post-delivery	• Clinic records • Electronic card system • Telephone survey 3 at 6 months after delivery
• Likelihood of a live birth and child survival 48 h after birth	• Clinic records • Telephone survey 2 at 2 weeks after EDD, if not delivered at the facility
• Likelihood of a maternal death during delivery and 48 h postpartum	• Clinic records • Telephone survey 2, 2 weeks after EDD, if not delivered at the facility
• Self-rated health of mothers, 6 months and 12 months after delivery	• Telephone surveys 1, 3 and 4 at 6 months and 12 months after delivery
• Mother’s perception of infant’s health, 6 months and 12 months after delivery	• Telephone surveys 2, 3 and 4 at 6 months and 12 months after delivery
• Proportion of mothers exclusively breastfeeding to 6 months of age	• Telephone surveys 2 and 3 and 4 at 6 months and 12 months after delivery
• Proportion of women using family planning and contraceptive use after delivery	• Telephone surveys #3 and #4 at 6 months and 12 months after delivery
• Screening and control of infections for mothers and fetus/baby during pregnancy and postnatal periods	• Clinic records (ANC, HF deliveries and PNC clinic records) • Manual collection of health records
• Cost of delivery and cost effectiveness of the intervention	• Project accounts • Key informant interviews • Facility costing tool
• Benefit incidence and equity impact of the intervention	• Clinic records • Electronic system • Telephone surveys 1, 2, 3, 4
Key confounders/covariates	Source of data
• Expected date of delivery • Education • Asset ownership • Age • Distance to facility • Level of health facility • Marital status • Number of children • Planned pregnancy • Quality of care (e.g. waiting time) • Migration away from study area	• Enrolment survey at health facility • Clinic records • Telephone survey 1, 3, 4
Key process indicators	Source of data
• Satisfaction with care received	• Telephone surveys 1, 2 and 3 at 2 weeks, 6 months and 12 months after delivery, focus group discussions with a sub-sample of participating women in the intervention area
• Health worker motivation	• Key informant interviews with health service providers
• Receipt of the *Afya* and/or any other transfers	• Telephone surveys 3 and 4 at 6 months and 12 months after delivery

*MNCH* maternal, newborn and child health, *ANC* antenatal care, *PNC* postnatal care, *EDD* expected delivery date

#### Data collection at enrolment

During enrolment, after written informed consent has been obtained, a trained nurse at the enrolling facility extracts background information from the participant’s health records and enters them into the card reader as described in section Card-reader system for automatic tracking of health visits and cash transfers. The extracted data include name, age, marital status, parity, stage of pregnancy, expected date of delivery (EDD), area of residence and mobile phone number.

#### Telephone surveys

Data are collected on secondary outcomes, socio-economic characteristics, care seeking and decision-making regarding the cash transfer, using the four follow-up telephone surveys described subsequently. Some data on the primary outcomes are also collected (see Table 1). The surveys are administered to all participants in both the intervention and control groups.

Telephone survey one: after enrolment

The first telephone interview is conducted with all participants as soon as possible after enrolment. This structured questionnaire collects data on socio-economic status, self-rated health and decision-making. Information on the recent health visit is also collected, including cost and time taken to travel to the facility, waiting time, cost of all care received and satisfaction with the care received. The same questionnaire is administered to the intervention and control groups, and the interviewer is blinded to the allocation of the participant.

Telephone survey two: 2 weeks after the EDD, if no facility delivery

A phone survey is conducted with all mothers who delivered babies at home, 2 weeks after their EDD. This survey collects information on delivery date, delivery outcome, who conducted the delivery, self-rated wellness for mother and child and breastfeeding initiation. The interviewer is blind to participant allocation.

Telephone survey three: 6 months after the EDD/child birth

A telephone survey is administered to 50% of participants 6 months after the EDD, to collect data on secondary outcomes such as maternal and child deaths, self-rated health of mothers and infants, exclusive breastfeeding and utilization of family planning methods. This survey also collects information on the last health care visit including the cost of seeking care, purpose of visit, waiting time and visit experience.

A second part of the survey is used to elicit information on the receipt of any conditional or unconditional cash transfer, receipt of *Afya* transfers (in the intervention arm only), how any money received was spent and who decided how the money was spent. The interviewer is not blind to participant allocation, as some questions are related to receipt and utilization of the cash transfers.

Telephone survey four: 12 months after the actual delivery date

A final survey is conducted with the same 50% of participants who completed telephone survey three. This survey again collects data on secondary outcomes such as maternal and child deaths, self-rated health, breastfeeding and utilization of family planning methods, information on the latest health care visit, and receipt and use of any cash transfers. Moreover, this survey collects additional information on complementary feeding and immunization. The interviewer is blind to participant allocation except for the final part that seeks information on receipt of cash transfers and its usage.

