#### Interim analysis and monitoring by the Data Management Committee (DMC)

We do not expect any adverse effects of the intervention but plan to carry out two interim analyses in 2018 and 2019, which will be reported to an independent Data Management Committee (DMC) to be convened according to the DAMOCLES charter [44]. For these meetings, the DMC will be provided with a report on the two key safety measures for the trial, presented separately by trial arm. The two key safety measures are infant and maternal mortality. The DMC will decide at each meeting whether to request further analyses, which may include analysis of the study primary outcomes, and will on each occasion recommend the study should either continue or stop. The DMC may also comment on whether any changes to the trial should be made, for example if the basis of the sample size calculation is contradicted by the accumulating data or if changes are required to improve recruitment or data capture. Only the trial statistician and the DMC will be aware of the outcomes on these safety measures.

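### Deaths to 48 h are sought by routes that differ with place of delivery, an outcome the cash is meant to change, and survey two does not fit the maternal-death outcome assigned to it

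*Protocol article*

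**What the plan says.** Table 1 (Data collection methods) lists two survival outcomes among the secondary outcomes: "Likelihood of a maternal death during delivery and 48 h postpartum" and "Likelihood of a live birth and child survival 48 h after birth". Both have the same two sources, clinic records and a conditional telephone call; for maternal death the entry is "Telephone survey 2, 2 weeks after EDD, if not delivered at the facility". No other survey is listed for either outcome.

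The Telephone surveys section heads this call "Telephone survey two: 2 weeks after the EDD, if no facility delivery" and then describes it: "A phone survey is conducted with all mothers who delivered babies at home, 2 weeks after their EDD". Its content is: "This survey collects information on delivery date, delivery outcome, who conducted the delivery, self-rated wellness for mother and child and breastfeeding initiation". Women who deliver in a facility do not receive it.

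Survey three, at 6 months in 50% of participants and regardless of place of birth, is there "to collect data on secondary outcomes such as maternal and child deaths", among other things. Survey four returns to the women who completed survey three. Table 1 cites neither for the two survival outcomes.

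Facility delivery is a primary outcome. On safety monitoring, the section on interim analysis and the DMC states: "The two key safety measures are infant and maternal mortality". These are reported to the DMC by arm.

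**The concern.** Two things do not fit together. First, whether a death is looked for only in clinic records, or in clinic records plus a call, is decided by where the woman gave birth. That is settled after randomization and is expected to differ between arms if the intervention works. Unequal detection by place of birth then becomes unequal detection by arm.

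Second, Table 1 makes survey two the added source for maternal death after a birth outside a facility, yet the survey as described is held with the mother and asks how well she feels. A woman who has died cannot answer it, her death is not a listed item, and nobody is named to answer for her. Clinic records are unlikely to show a death at home. In the other direction, clinic records after a facility birth may not show a death that occurs once the woman has left.

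What is at stake is the two secondary survival outcomes and, if the same sources feed the DMC report, the early part of the two mortality measures on which the DMC advises whether to continue. These events are few, so incomplete counting matters as well as any distortion of the comparison.

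**Working it through.** The protocol gives no figure for how completely deaths are found. Its only related arithmetic is the design effect for the attendance outcomes. That reproduces (1 + 149 × 0.005 = 1.745 and 3600 / 1.745 = 2063; 1 + 149 × 0.025 = 4.725 and 3600 / 4.725 = 762) and is not affected by this point.

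**Planned sources side by side**

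| | Facility birth | Other birth |
|---|---|---|
| Clinic records | listed | listed |
| Survey two | not held | listed, without a vital-status item |
| Survey three (50% of women) | collects deaths, not listed in Table 1 | collects deaths, not listed in Table 1 |

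**Inputs**
- Women per arm: 24 × 150 = 3600 (Sample size).
- Births outside a facility, control arm: h_C = 1 − 0.696 = 0.304. This uses skilled attendance in the county (Study setting) as a stand-in for facility delivery.
- Shift due to the intervention: 4.5 or 7.5 percentage points, the detectable differences at 50% prevalence (Sample size), so h_I = 0.259 or 0.229.
- Assumed, not in the protocol: the share of deaths found after facility birth (s_F) and after home birth (s_H), and the ratio r of death risk at home to that in a facility.

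**Formula**

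Recorded risk in an arm is proportional to s_F(1 − h) + s_H·r·h. The observed ratio is the intervention value divided by the control value.

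**Observed ratio when the true ratio is 1.00 (r = 1)**

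| s_F | s_H | 4.5-point shift | 7.5-point shift |
|---|---|---|---|
| 1 | 0 | 0.741/0.696 = 1.065 | 0.771/0.696 = 1.108 |
| 1 | 0.25 | 1.044 | 1.073 |
| 1 | 0.5 | 1.027 | 0.8855/0.848 = 1.044 |
| 1 | 0.75 | 1.012 | 1.020 |
| 1 | 1 | 1.000 | 1.000 |
| 0.7 | 1 | 0.7777/0.7912 = 0.983 | 0.7687/0.7912 = 0.972 |

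The last row is the reverse case, in which facility records miss deaths and the home route misses none.

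If home risk were twice facility risk (r = 2) and no home death were found, with a 7.5-point shift, the true ratio would be (0.771 + 2 × 0.229)/(0.696 + 2 × 0.304) = 1.229/1.304 = 0.942. The observed ratio would be 1.108.

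**Under-count**

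Take 30% and 22.5% home births, full capture after facility birth, and an assumed 48 h risk of 0.4%, so 3600 × 0.004 = 14.4 true deaths per arm.
- Half of home deaths missed: control 14.4 × 0.85 = 12.24 (15% lost), intervention 14.4 × 0.8875 = 12.78 (about 11% lost). Ratio 1.04.
- All missed: control 14.4 × 0.70 = 10.08 (30% lost), intervention 14.4 × 0.775 = 11.16 (22.5% lost). Ratio 1.11.

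**Scale**

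At the county's 695 per 100,000, 3600 women give 25.0 maternal deaths per arm over the whole maternal period. At equal risk, 25.0 × 0.304 = 7.6 of these in the control arm would follow a birth outside a facility. Deaths within 48 h would be fewer.

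With 12.24 and 12.78 recorded deaths, the standard error of the log ratio is √(1/12.24 + 1/12.78) = 0.40. The 95% interval therefore extends by a factor of exp(1.96 × 0.40) = 2.2 each way, before any allowance for clustering.

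**The case against.** A reader might infer that a maternal death after a home birth can be recorded only by interviewing the mother. The document does not support that. Clinic records are listed as well and are not confined to facility births. Survey three collects maternal and child deaths in half the women. The eligibility criteria allow the contact phone to belong to a household member or trusted person, who might answer. The heading of survey two covers any woman without a facility delivery, so a woman who died at home is in the group to be called. A survey that records maternal deaths at all, as surveys three and four do, must accept another respondent. This stands against the word only. It does not turn survey two as described into a record of vital status, and none of these safeguards makes the planned sources the same for both places of birth.

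A reader might also infer that deaths are in fact missed, or that the bias runs in a known direction. Neither is shown. The protocol does not say when women leave a facility or how later deaths are learned of, and if facility records are the weaker source the bias reverses.

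Nor does the document show harm being hidden from the DMC. It does not say which sources feed that report, infant and maternal mortality are wider than 48 h survival, and the scenarios with missed home deaths make the intervention look worse, not better.

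The respondent rule and call codes could reasonably sit in a field manual that is not shown. That is fair for the detail. But the source list in Table 1 and the description of survey two are stated in the article, and they do not match the outcome they serve. Finally, a distortion of a few percent is small beside a sampling interval of a factor of 2.2. That stands, and it limits the weight of the point.

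**Conclusion.** The point holds in a limited form. As written, early deaths are sought by different routes according to place of delivery, which the intervention is meant to change, and survey two is poorly matched to the maternal-death outcome that Table 1 gives it. Deaths at home may be under-recorded, and facility records may miss deaths after the woman leaves. The document fixes neither the size nor the direction of the bias.

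The ranges in the brief rest on assumed capture rates, on skilled attendance standing in for facility delivery and, apart from the one r = 2 case, on equal risk by place of birth. The distortion of the ratio is modest. The possible loss of events is the larger concern, because safety events are few. The attendance outcomes and the sample size are untouched. The change is worth making mainly because it uses calls and death data already planned.

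**What to change.** - **Survey two:** record the vital status of mother and baby at 48 h from whoever answers the contact phone. Code an unanswered call as unknown, not as alive.
- **Table 1:** list survey three as a source for both survival outcomes, for home and facility births alike, with the date of death so that the 48 h limit can be applied. Survey four adds little for early maternal deaths, since it reaches only women who completed survey three.
- **DMC report:** include deaths found by these routes, and show unknown vital status by arm.
- **Analysis:** add a sensitivity analysis restricted to the survey three half with survey three as the source, where the route does not depend on place of birth.

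The cost is a line in the call script, a table edit and one extra analysis. Proxy reports are less precise, especially on timing, and survey three covers only half the women, so detection becomes more even but not identical in the whole sample. Recruitment closed on 31 July 2018 and the protocol version is dated 26 December 2018, so many survey two calls have probably been made. For those women the survey three, reporting and analysis changes are the ones that can still help.

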### Data management and analysis

#### Blinding

Due to the nature of the intervention, participants are not blinded to their study allocation. Some data collection is, however, blinded to the intervention allocation status of participants as described in the data collection section. Project managers are not blinded to the allocation status of the study participants; however, the Principal Investigators and analysts will remain blinded. Data will be analysed blinded to the intervention status of participants.

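### As written, the 6-month survey interviewer is unblinded without limit, although the stated reason covers only the cash-transfer part and the 12-month survey stays blind until that part

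*Protocol article*

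**What the plan says.** The Telephone surveys section of the protocol article describes interviewer blinding separately for each of four surveys.

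- **Survey one** (after enrolment): "the interviewer is blinded to the allocation of the participant".
- **Survey two** (2 weeks after the EDD, if there was no facility delivery): "The interviewer is blind to participant allocation".
- **Survey three** (6 months after the EDD, half of participants) is used "to collect data on secondary outcomes such as maternal and child deaths, self-rated health of mothers and infants, exclusive breastfeeding and utilization of family planning". The next paragraph adds: "A second part of the survey is used to elicit information on the receipt of any conditional or unconditional cash transfer". That paragraph ends: "The interviewer is not blind to participant allocation, as some questions are related to receipt and utilization of the cash transfers".
- **Survey four** (12 months after delivery, the same half): "This survey again collects data on secondary outcomes such as maternal and child deaths, self-rated health, breastfeeding and utilization of family planning methods". On blinding: "The interviewer is blind to participant allocation except for the final part that seeks information on receipt of cash transfers and its usage".

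The Blinding section says: "Due to the nature of the intervention, participants are not blinded to their study allocation". For data collection it refers back to the survey descriptions and gives no further reason for treating survey three differently.

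**The concern.** Survey three is the only one of the four whose interviewer is described as not blind with no exception. The single reason given concerns cash-transfer questions, which sit in their own part of the questionnaire. Survey four has the same mix of outcome and cash questions and protects the outcome part, so the protocol itself shows that the reason does not require unblinding during the outcome questions.

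The outcomes at stake are listed secondary outcomes that rest on a woman's answer and on how the interviewer probes and codes it: her own health, her infant's health, exclusive breastfeeding and contraceptive use. Survey three is also the survey timed to the 6-month breastfeeding endpoint. An interviewer who knows the arm can probe or code differently by arm. If that happens at 6 months and not at 12, a change in the estimated effect between the two time points may partly reflect how the data were collected.

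**Working it through.** **1. The two surveys side by side**

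| | Survey three (6 months) | Survey four (12 months) |
|---|---|---|
| Women | 50% of participants | The same 50% |
| Outcomes | Deaths, self-rated health, breastfeeding, family planning | The same kinds, plus complementary feeding and immunization |
| Cash questions | Separate second part | Final part |
| Interviewer | Not blind; no part excepted | Blind except in the final part |

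The structure is the same and the blinding differs. Nothing elsewhere in the article explains the difference.

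**2. The protocol's own precision figures**

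Inputs from Sample size: 24 clusters per arm, m = 150 per cluster, ICC 0.005 or 0.025. Formulas: DE = 1 + (m − 1) × ICC; ESS per arm = 24 × m / DE.

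- ICC 0.005: DE = 1 + 149 × 0.005 = 1.745; ESS = 3600 / 1.745 = 2063.
- ICC 0.025: DE = 1 + 149 × 0.025 = 4.725; ESS = 3600 / 4.725 = 762.

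Both match the protocol. Its detectable values from 50% (54.5% and 57.5%) have power of 82.5% and 83.6%, so they look rounded up to the next half point.

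**3. The same calculation for the survey-three subsample**

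Assumption: half of 150, so m = 75 per facility and 3600 women in all, before losses and non-response.

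- ICC 0.005: DE = 1 + 74 × 0.005 = 1.37; ESS = 1800 / 1.37 = 1314 per arm.
- ICC 0.025: DE = 1 + 74 × 0.025 = 2.85; ESS = 1800 / 2.85 = 632 per arm.

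Difference detectable from 50% with 80% power, two-sided 5%, is about 2.80 × √(0.5 / ESS):

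- ICC 0.005: 2.80 × √(0.5 / 1314) = 0.055. Using each arm's own variance it is 0.054.
- ICC 0.025: 2.80 × √(0.5 / 632) = 0.079. Using each arm's own variance it is 0.078.

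The range is therefore about 5.4 to 7.9 points.

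**4. What an interviewer effect could do (illustration only)**

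The documents give no figure, so 2 to 3 points is an assumption. As a share of the detectable difference it is 2/5.5 = 36% to 3/5.5 = 55% at ICC 0.005, and 2/7.9 = 25% to 3/7.9 = 38% at ICC 0.025.

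With no true effect and 50% prevalence, the chance of a significant result in the direction of a bias b is Φ(b / SE − 1.96), where SE = √{[0.25 + p(1 − p)] / ESS} and p = 0.5 + b. Without bias it is 2.5%.

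| Assumed bias | ICC 0.005 | ICC 0.025 |
|---|---|---|
| 2 points | 17.5% | 10.6% |
| 3 points | 33.7% | 18.6% |

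**5. Timing**

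Trial status gives recruitment from 15 July 2017 to 31 July 2018 and a protocol version dated 26 December 2018. Six months before that date is 26 June 2018. Women with an EDD before then had already reached their 6-month call; those with a later EDD, including women still pregnant when enrolled in July 2018, had not. So at that version date some calls could have been made and others were still to come.

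**The case against.** The strongest reply is that the survey-three sentence closes the paragraph on the second part, while the outcome questions are in the paragraph before. It may have been meant for that part alone, which would match survey four. This stands as a possibility. A reader might infer that the whole call is certainly unblinded, but the text does not prove that. Unrestricted non-blinding is still the natural reading, because survey four states its exception explicitly and survey three states none. On either reading the sentence needs correcting.

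Four further points limit the concern:

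- **Respondents know their arm and report these outcomes themselves.** Blinding the interviewer removes differential probing and coding, not respondent bias, and a woman may reveal her arm during the call. The same holds for surveys one, two and four, where interviewers are nevertheless blinded.
- **Reach into the primary analysis.** A reader might infer that biased survey-three answers feed the imputation of visits outside the study area. The documents do not go that far. The section on visits outside the study area puts primary-outcome questions into the surveys given to 50% of participants without assigning them to survey three. The survey-three description mentions only the last visit. Final analysis makes imputation conditional and prefers to avoid it. If such questions are asked in survey three and imputation is triggered, the imputed analysis becomes primary and the point would reach it.
- **Comparability.** It would be too strong to call the 6- and 12-month results non-comparable. A possible interviewer effect at one time point weakens the comparison without voiding it.
- **Deaths**, also asked about in survey three, are less exposed.

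**Conclusion.** The concern holds in a limited form. The protocol leaves the survey-three interviewer unblinded without limiting this to the cash-transfer part. Its reason covers only that part, and its own survey four shows that the outcome questions can be asked blind. The consequence is an avoidable risk of interviewer bias in four self-reported 6-month secondary outcomes and weaker comparability with 12 months. An effect on the primary analysis is conditional and not established.

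The size cannot be determined from the documents. The detectable difference of 5.4 to 7.9 points assumes 75 women per facility, 50% prevalence and no losses; fewer women would raise it and lower the share that a given bias represents. The 2 to 3 point interviewer effect is assumed. The non-blinding is openly disclosed and the outcomes are secondary, so this is a worthwhile, inexpensive improvement and not a threat to the trial's main conclusion.

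**What to change.** 1. For the survey-three calls that remain, follow the survey-four procedure: keep allocation off the call sheet, complete and lock the outcome sections first, and reveal the arm only when the cash-transfer part opens.
2. If only the second part was ever meant to be unblinded, amend the sentence to say so.
3. Flag interviews whose outcome section was completed by an unblinded interviewer, and report this as a limitation of the 6-month results.
4. State whether survey three carries the primary-outcome visit questions, so that any bearing on imputation is known.

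The cost is a change in question order and call sheet, plus a sentence or two of text. No extra staff or calls are needed. Calls already made cannot be re-blinded, so for those only flagging and disclosure are possible.
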